## Treatment Assignment

- All patients will be offered home hospitalization.
- If patient/caregiver does not consent, the research assistant will ask the patient's permission to collect covariates, functional status, and a quality of life measure to determine generalizability of enrollment.

As an amendment to our current protocol, patients will be randomized (random sized blocks between 3 and 6 stratified by infection, heart failure, COPD/asthma, and other with concealed allocation) to remote care (intervention) versus in-person care (control) at the time of enrollment. Once 210 patients have been enrolled in this schema (see power calculations below), and if remote care is noninferior to in-person care, we will allow remote care to continue as a single arm while continuing other concurrent experiments.

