| MRSA                                   | As above.                                                                                                                                                                       | Daily     |
| Transfer back to hospital a | RA via MD/RN                                                                                                                                                                    | Discharge |
| All-cause mortality during admission   | RA via MD/RN for home patients; MD EHR review for inpatients                                                                                                                    | Discharge |
| Unplanned mortality during admission   | RA via MD/RN for home patients; MD EHR review for inpatients                                                                                                                    | Discharge |
| All-cause 30-day mortality             | RA via pt/caregiver call                                                                                                                                                        | +30       |
| Unplanned 30-day mortality             | RA via pt/caregiver call                                                                                                                                                        | +30       |
| Heart Failure                   |                                                                                                                                                                                 |           |
| New arrhythmia                         | RA via MD/RN for home patients; MD EHR review for inpatients                                                                                                                    | Daily     |
| Hypokalemia                            | As above.                                                                                                                                                                       | Daily     |
| Acute kidney injury                    | As above.                                                                                                                                                                       | Daily     |

a: intervention arm only

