### *Remote vs In-Person Physician Care*

In a randomized controlled non-inferiority trial, we will test an in-person daily physician visit (“in-person care;” control) vs a daily physician visit conducted remotely via video facilitated by a care team member (“remote care;” intervention) for acutely ill patients who are home hospitalized. The primary outcome (dependent variable) is number of adverse events during the acute episode of care (see “Summarizing Adverse Events” table below). The primary predictor (independent variable) is study arm (in-person care vs remote care). We will assess the non-inferiority of the primary outcome with a generalized linear model using Poisson distribution, given the primary outcome is count data. Although we have multiple covariates of interest, we are cognizant of over adjustment. We plan to adjust for age, gender, race/ethnicity, PRISMA-7, education, and HOSPITAL score). We may include additional covariates if groups have significant differences at baseline.

Because patients in the intervention arm will receive at least some of their intervention through a “change agent” (in this case, a Home Hospital team) shared with other participants, we need to account for this in the analysis. We will therefore cluster by Home Hospital physician using general estimating equations.

Other outcomes will be analyzed in a similar manner, using Poisson regression for other “count” outcomes (e.g., number of new or worsening signs or symptoms per patient, days at home since discharge), multivariable logistic regression for binary outcomes (e.g., 30-day readmission, ED visit, PCP

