#### Summarizing Adverse Events

| Measure                                     |
|---------------------------------------------|
| Fall                                        |
| Delirium                                    |
| Potentially preventable VTE                 |
| New pressure ulcer                          |
| Thrombophlebitis at peripheral IV site      |
| CAUTI                                       |
| New Clostridium difficile                   |
| New MRSA                                    |
| New arrhythmia                              |
| Hypokalemia                                 |
| Acute kidney injury                         |
| Transfer back to hospital                   |
| Mortality (unplanned) during admission      |
| Mortality (unplanned) 30-day post-discharge |

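### The safety-table footnote limiting transfer back to hospital to the intervention arm conflicts, as worded, with the remote-care trial's primary adverse-event count, which needs transfers from both arms

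*Protocol*

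**What the plan says.** - **Safety table** (under Data to be collected). The transfer-back row carries footnote a: "intervention arm only". Its source is the research assistant via physician or nurse. Most other rows use a two-part source: "RA via MD/RN for home patients; MD EHR review for inpatients".
- **Treatment Assignment.** Patients are randomised "to remote care (intervention) versus in-person care (control) at the time of enrollment".
- **Remote vs In-Person Physician Care.** The trial is "for acutely ill patients who are home hospitalized", and its primary outcome "is number of adverse events during the acute episode of care", taken from the Summarizing Adverse Events table.
- **Summarizing Adverse Events.** The list includes "Transfer back to hospital" with no limit to one arm.
- **Power analysis, Remote vs In-Person Care Analysis.** The margin is 0.1 events, the baseline is 0.09 (SD 0.29), alpha is 0.025 and power is 80%. The size is 210 before and 260 after clustering. A futility look after 130 patients stops the trial if the remote arm is higher by 0.10 or more.

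**The concern.** The footnote makes sense where the comparator is a hospital ward, since an inpatient cannot be sent back. It does not fit the randomised comparison. There, in-person patients are also at home, and the Standard Operating Procedure for Problematic Situations sends patients back without regard to arm. The protocol's other uses of the term intervention arm lie in the description of the daily physician interaction, the analysis section of the randomised trial and its futility rule. In each of these places it denotes the remote arm.

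A research assistant who follows the table as worded would therefore record transfers for remote patients only, while the primary count needs them from everyone. The result would be arm-dependent ascertainment of a primary-outcome component, carried into both the futility look and the final test.

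**Working it through.** **1. The plan's own sample size.** The inputs are margin 0.1, SD 0.29, true difference 0 and power 80%, with n per arm = 2 × SD² × (z₁₋α + z₀.₈₀)² / margin².
- One-sided 0.05: 2 × 0.0841 × (1.645 + 0.842)² / 0.01 ≈ 104 (105 with the t distribution). This matches the stated 105.
- One-sided 0.025: 2 × 0.0841 × (1.960 + 0.842)² / 0.01 gives 133, which does not match.
- Clustering: 130 per arm over 5 physicians is 26 per cluster, so the design effect is 1 + 25 × 0.01 = 1.25, and 104 × 1.25 = 130. This matches the stated 130.

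The stated alpha is 0.025 but the size reproduces at one-sided 0.05, so both levels are carried below.

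**2. Size of the distortion.** The Appendix (Selected Safety data to-date) gives 5 transfers in 203 home patients: 5/203 = 0.0246 per patient. If both arms truly have this rate and only the remote arm's transfers are recorded, the expected difference is +0.0246 against remote care. Relative to the margin, that is 0.0246/0.10 ≈ 25%.

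**3. Chance of showing non-inferiority.** The effective size is 130/1.25 = 104 per arm, so SE = 0.29 × √(2/104) = 0.0402. Power = Φ((0.10 − d)/SE − z₁₋α), where d is the bias.

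| d | one-sided 0.025 | one-sided 0.05 |
|---|---|---|
| 0 | 70% | 80% |
| 0.01 (assumed) | 61% | 72% |
| 0.0246 (5/203) | 47% | 59% |
| 0.05 (assumed) | 24% | 34% |

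Without the design effect, at 130 per arm and one-sided 0.025, the figures for d = 0 and d = 0.0246 are about 79% and 55%. The protocol presents 130 as the size inflated for clustering, so the table above is the fairer basis.

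**4. False futility stop.** At 65 per arm, without a design effect, SE = 0.29 × √(2/65) = 0.0509. P(observed difference ≥ 0.10) = 1 − Φ((0.10 − d)/SE).
- d = 0: about 2.5%
- d = 0.0246: about 7%
- d = 0.01 to 0.05 (assumed): about 4% to 16%

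**5. If transfers are scored in both arms.** The expected difference under equal care returns to 0 and the d = 0 figures apply.

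**The case against.** The best defence is that, in context, the footnote means home patients as opposed to inpatients, and there is good evidence for this.
- The Safety table serves several comparisons. Its source column contrasts home patients with inpatients, never remote with in-person, and the transfer row gives only the home half of the usual source.
- Study endpoints calls the home cohort in the non-randomised comparison an intervention group. Safety monitoring and the Appendix note also use intervention for home hospital care.
- Safety monitoring says the committee cannot be blinded to a transfer. That fits home versus ward but not remote versus in-person.
- Treatment Assignment introduces the randomisation as an amendment, so the footnote is plausibly text that was not revised.

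Other sections would also bring in-person transfers to light. The primary count lists transfer without restriction, and Safety monitoring and Adverse event reporting guidelines send transfers to the committee whatever the arm.

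This stands as an account of origin, and it makes full loss of the in-person transfers less likely. It rules out the stronger reading that a reader might take from the footnote, that only one randomised arm can score the item and the primary comparison is therefore biased. In-person patients can be transferred, and nothing shows that the footnote was applied literally in the trial. It does not remove the conflict, because the current wording uses a term that elsewhere means the remote arm.

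The direction also limits the harm: literal use works against remote care, so it makes non-inferiority harder to show and cannot produce a false claim of it. Nor should the Appendix be used to state transfers as a share of all primary events, since it is a selection that omits falls, hypokalemia and acute kidney injury.

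**Conclusion.** The point holds as an internal conflict between a stated collection rule and the definition of the randomised trial's primary outcome. It does not hold as a demonstrated bias.

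Under literal use, the bias would be about 0.025 events per patient against remote care. The chance of showing non-inferiority would fall by about 23 points at one-sided 0.025 (70% to 47%) or 21 points at one-sided 0.05 (80% to 59%), and the chance of a false futility stop would rise by 4 to 5 points. Partial use would give a smaller bias whose size cannot be estimated from the document.

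These figures assume equal true event rates, a transfer rate of 5/203 in both arms, an unchanged SD of 0.29 and a normal approximation to what the plan will analyse by clustered Poisson regression. The protocol does not say whether its 0.09 baseline includes transfers. Since the correction is nearly free and the item feeds the primary endpoint, it should be made, preferably before the 130-patient look.

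**What to change.** Reword footnote a along these lines: *home-hospital patients only, in both arms of the remote versus in-person trial; not applicable to traditional-hospital controls*. State that transfers are collected and counted identically in the remote and in-person arms, for the interim difference and for the final analysis, in line with Summarizing Adverse Events.

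The cost is one footnote and one line on the data-collection form. The home team already knows of the event in both arms, and no clinical rule changes. If patients have already been randomised, check the in-person arm's transfers against the reports to the monitoring committee before the futility look.

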#### Quality: High-Value Care

| Measure                                 | Source                                                       | Day(s) Obtained |
|-----------------------------------------|--------------------------------------------------------------|-----------------|
| Pain management                         | RA via MD/RN for home patients; RA EHR review for inpatients | Daily           |
| Hours of sleep per day                  | RA via activity tracker                                      | Daily           |
| Hours of sleep per night                | RA via activity tracker                                      | Daily           |
| Hours of activity per day               | RA via activity tracker                                      | Daily           |
| Hours of activity per night             | RA via activity tracker                                      | Daily           |
| Hours of sitting upright per day        | RA via activity tracker                                      | Daily           |
| Hours of sitting upright per night      | RA via activity tracker                                      | Daily           |
| Daily steps                             | RA via activity tracker                                      | Daily           |
| Pneumonia                        |                                                              |                 |
| Pneumococcal vaccination if appropriate | RA via EHR                                                   | Discharge       |
| Influenza vaccination if appropriate    | RA via EHR                                                   | Discharge       |

|                                                                                  |                                                                             |                |
|----------------------------------------------------------------------------------|-----------------------------------------------------------------------------|----------------|
| Smoking cessation counseling if appropriate                                      | RA via EHR                                                                  | Discharge      |
| Heart Failure                                                             |                                                                             |                |
| Evaluation of ejection fraction scheduled or completed if not done within 1 year | RA via EHR                                                                  | Discharge      |
| ACEI/ARB for HFrEF (EF < 40%)                                                    | RA via EHR, pt (post discharge)                                             | Discharge, +30 |
| Beta blocker for HFrEF (EF < 40%)                                                | As above.                                                                   | Discharge, +30 |
| Aldosterone antagonist for HFrEF (EF < 40%)                                      | As above.                                                                   | Discharge, +30 |
| Lipid lowering for CAD, PVD, CVA, or diabetes                                    | As above.                                                                   | Discharge, +30 |
| Smoking cessation counseling if appropriate                                      | As above.                                                                   | Discharge      |
| Smoking status post-discharge                                                    | RA via pt                                                                   | +30            |
| Glucose                                                                   |                                                                             |                |
| Patient-days with glucose between 70mg/dL and 180mg/dL                           | Dexcom device and EHR                                                       | Daily          |
| Patient-days with glucose > 300mg/dL                                             | Dexcom device and EHR                                                       | Daily          |
| Patient-days with glucose < 70mg/dL                                              | Dexcom device and EHR                                                       | Daily          |
| Patient-days with glucose < 40mg/dL                                              | Dexcom device and EHR                                                       | Daily          |
| Patient-day weighted mean glucose                                                | Average all readings for one day, then average the averages across all days | Daily          |
| Any glucose >300mg/dL, y/n                                                       | Dexcom device and EHR                                                       | Daily          |
| Any glucose <70mg/dL, y/n                                                        | Dexcom device and EHR                                                       | Daily          |
| Any glucose <40mg/dL, y/n                                                        | Dexcom device and EHR                                                       | Daily          |
| Capillary versus continuous glucose (see statistical methods)                    | Dexcom device and EHR                                                       | Daily          |

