  - To improve our ability to monitor and care for patients who have glycemia concerns, we will begin using the Dexcom G6. This will provide our clinicians continuous glucose measurements and predictive glucose alerts (signaling hypoglycemia or hyperglycemia), while reducing finger stick glucose checks.
  - Any patient who the home hospital physician believes would benefit from continuous glucose monitoring, will receive the Dexcom G6 during their home hospital stay.
  - Although the Dexcom G6 is FDA cleared, the transmitter's cleaning procedure is not. The Dexcom G4 (a highly similar unit) does have an FDA approved cleaning procedure. We propose (upon recommendation of Dexcom) to use this cleaning procedure with the Dexcom G6 (see procedure attached as separate document). The sensor that inserts into the patient is single-use only.
  - This device will never interact with Brigham computer systems, never be programmed with protected health information, and never be used in the hospital.
- Blood alcohol content breathalyzer: BACtrack S80 Pro (FDA cleared application/use)

- We would like the ability to perform point of care testing for blood alcohol content.
- We plan to use the FDA-cleared BACtrack S80 Pro, manufactured by BACtrack.
- This is a free-standing device that has no send/receive capability, will never interact with Brigham computer systems, never be programmed with protected health information, and never be used in the hospital.
- Virtual physical therapy
  - Prior literature has shown that movement is paramount to healing and maintaining health. We would like the ability to offer more intensive physical therapy to our home hospital patients with the use of a virtual physical therapy system called VeraHome, created by Reflexion Health.

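### Glucose excursion measures combine continuous sensor and chart readings, but only selected home patients can wear the sensor, so comparisons with traditional-hospital controls are biased toward more recorded excursions at home

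*Protocol*

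**What the plan says.** The Glucose block of the Protocol's Quality: High-Value Care table lists patient-day measures (for example "Patient-days with glucose < 70mg/dL") and yes/no measures (for example "Any glucose <70mg/dL, y/n") at <70, <40 and >300 mg/dL, plus patient-days between 70 and 180 mg/dL. The source entry for each is "Dexcom device and EHR".

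Devices to be used describes the sensor:
- Who wears it: "Any patient who the home hospital physician believes would benefit from continuous glucose monitoring, will receive the Dexcom G6 during their home hospital stay".
- What it yields: "This will provide our clinicians continuous glucose measurements and predictive glucose alerts", and it does so "while reducing finger stick glucose checks".
- Where it is not used: "This device will never interact with Brigham computer systems, never be programmed with protected health information, and never be used in the hospital".

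The Secondary Aims include maintaining or improving quality of care for patients who would otherwise be admitted, and point to the measure tables for definitions and sources. Under Statistical methods, the home-versus-traditional-hospital analysis weights by propensity score on the covariates of interest, baseline functional status and DRG. Early transfer uses the same analysis. The Continuous Glucose Monitoring Analysis covers only agreement between meter and sensor.

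**The concern.** A yes/no measure of whether any reading crossed a threshold, or a count of days with such a reading, depends on how often glucose was read as well as on glucose itself. Sensor wearers at home are read continuously. Traditional-hospital controls can contribute only the intermittent values in their charts. The two groups would be scored with different instruments at very different sampling rates.

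At stake is the reading of the quality-of-care aim. Home hospital could appear to control glucose worse than the ward solely because it looks more often. If sensor alerts truly prevent excursions, the same artefact could hide that benefit.

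**Working it through.** **Direction, from the Protocol alone.** An indicator of at least one reading beyond a limit cannot fall, and normally rises, as readings are added to the same glucose course. The same holds for each patient-day. Sensor wearers have many more readings than controls, so with equal glucose control the expected difference is more recorded excursions at home. The propensity model balances patient characteristics. It contains no term for method or frequency of glucose measurement, and weighting could not create sensor readings for controls.

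**The plan's own figure.** There is none. The Protocol gives no rate, effect size or power for a glucose measure, no number of sensor readings or finger sticks per day, and no share of home patients who wear the sensor. Every input below is an assumption.

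**Size among wearers.** Both groups follow one log-normal, autocorrelated glucose process:
- mean 150, 180 or 210 mg/dL
- coefficient of variation 25, 30 or 35%
- correlation time 1.5 or 3 h
- between-patient log-SD 0.15
- 4-day stay and no sensor error

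The same process is read every 5 minutes (sensor) or 4 times a day (chart). R is the sensor proportion divided by the chart proportion.

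| Measure | Range of R |
|---|---|
| Any <70 | 2.5 to 14.5 |
| Patient-days with a value <70 | 4.3 to 18.8 |
| Any >300 | 1.3 to 5.4 |
| Patient-days with a value >300 | 2.3 to 9.0 |

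Two scenarios for any <70, both with CV 30% and correlation time 3 h:
- Mean 150: 16.5% (chart) against 58.4% (sensor); 58.4 / 16.5 = 3.5.
- Mean 180: 4.6% against 26.8%; 26.8 / 4.6 = 5.8.

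The largest <70 ratios come from scenarios where the chart proportion is only about 1 to 3%, so the upper end is imprecise. Values <40 are too rare in most scenarios for a stable ratio.

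**Size across the home group.** Let f be the share of at-risk home patients who wear the sensor and c the chart-based proportion. If wearers and non-wearers have the same underlying glucose, the home proportion is f·R·c + (1 − f)·c. Dividing by c gives a ratio of 1 + f(R − 1).

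| f | Any <70 | Any >300 |
|---|---|---|
| 25% | 1 + 0.25 × 1.5 = 1.4 to 1 + 0.25 × 13.5 = 4.4 | 1 + 0.25 × 0.3 = 1.1 to 1 + 0.25 × 4.4 = 2.1 |
| 50% | 1 + 0.5 × 1.5 = 1.8 to 1 + 0.5 × 13.5 = 7.8 | 1 + 0.5 × 0.3 = 1.2 to 1 + 0.5 × 4.4 = 3.2 |

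**Other glucose rows.** For patient-days between 70 and 180 mg/dL the direction depends on a definition the table does not give. If all readings must be in range, more readings lower the count; if one suffices, they raise it. Patient-day weighted mean glucose averages within each day first, so extra readings do not inflate it in this way, and no bias is shown for it.

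**After the fix.** With both groups scored on intermittent readings at the same frequency, the expected ratio under identical control is 1.0, apart from sensor-versus-meter error.

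**The case against.** The strongest reply is that the faulty comparison is partly inferred. Glucose is not a primary or secondary endpoint of any of the four studies in the Study endpoints table. The source entry names where data come from and does not say how readings become an outcome, a detail that an analysis plan may settle. The only glucose analysis the Protocol spells out is meter-sensor agreement.

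The endpoint part stands and limits the weight of the point. The rest does not remove it. The Secondary Aims tie these tables, sources included, to the quality aim against usual admission, and the Protocol fixes a source that is unequal between those groups. Following it as written produces the bias.

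Four stronger readings are tempting and are not supported:
- *Home hospital as a whole would show several-fold more excursions.* That depends on the unstated share of wearers. At 25% wear, the ratio for any >300 is about 1.1 to 2.1, and for any <70 it can be as low as 1.4.
- *The remote-versus-in-person RCT is biased too.* Both arms are at home with the same access to the sensor, so device access creates no bias there.
- *The paramedic comparison is distorted.* Both groups are home patients. Distortion would need sensor use to differ between them, and nothing in the Protocol says it does.
- *The sensor is inaccurate.* Devices to be used says that sensing in the acute setting has been shown to be safe and accurate, with further testing under way. The bias arises even with a perfect sensor.

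**Conclusion.** The point holds for comparisons of home hospital or early transfer with traditional-hospital controls, on the patient-day and any-reading measures at <70, <40 and >300 mg/dL. The direction follows from the Protocol's own text. The size does not: the ratios rest on the assumed glucose distribution, 4-day stay, 5-minute sensor reading, 4 chart checks a day and share of wearers. Among wearers the excess for <70 mg/dL is plausibly several-fold; for >300 mg/dL, or when diluted over the home group, it can be well under twofold. The calculation also leaves out that physicians choose who wears the sensor. Because these are quality measures and not named endpoints, this should be corrected before analysis but does not threaten the trial's main conclusions.

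**What to change.** For every comparison against traditional-hospital controls, derive the threshold and patient-day measures from intermittent readings at comparable frequency in both groups. Use EHR capillary and laboratory values. For sensor wearers whose checks were dropped, add sensor values sampled at the check frequency observed in the controls' EHR data. Report measures from the full sensor trace only descriptively, among wearers. State whether a patient-day counts as between 70 and 180 mg/dL when all readings, or any one reading, are in range. Amend the source column of the Glucose rows to match.

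The cost is a change of analysis wording and of the source column; patient care is untouched. The downside is fewer readings per patient in the comparison, and some residual sensor-versus-meter error where sampled sensor values stand in for finger sticks.
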